## Abstract

**Background:**

Chronic Suppurative Otitis Media (CSOM) is the commonest cause of preventable deafness, affecting 164 million people worldwide, 90 % of whom live in low resource countries, such as Nepal. Simple, inexpensive treatment of acute otitis media can prevent the development of CSOM and its sequelae: deafness, abscess, encephalitis, and, rarely, death. CSOM is a disease of poverty and its social determinants: low parental education, overcrowding, poor hygiene and malnutrition. Previous studies have established economic, socio-cultural and geographic barriers to care seeking for childhood illness in the developing world and, in particular, in Nepal. The ultimate aim of this research is to improve the ear health of the children in Jumla, Nepal. The primary outcome is an increase in mother’s knowledge, attitude and practice regarding ear disease in their children. The secondary outcome is a reduction in the prevalence of CSOM in their children.

**Methods/design:**

Using 56 existing women’s self-help groups, sample size, adjusting for clustering and data analysis, is set at 15 groups per arm. A baseline survey of 30 randomly selected groups will be performed, consisting of a knowledge, attitude and practice questionnaire aimed at women who participate in self-help groups, as well as examination of their children’s ears. This will be followed by random allocation, stratified by geography, into 15 intervention and 15 control groups. The intervention groups will participate in three interactive educational sessions at their regular monthly meetings based on *World Health Organisation Primary Ear and Hearing Resource, Basic Level.* The control groups will continue their usual monthly group meetings. At 12 months, a follow-up assessment of both control and intervention groups will be performed, with a repeat women’s survey and repeat ear examination of the children. Data analysis will be by intention to treat and clustering will be considered at every stage. Cluster level data will be analysed using *t*-test and individual level data using mixed effects linear regression and logistic regression random effects model as appropriate.

**Discussion:**

Despite its remote location, Jumla has a vibrant network of health posts and community workers. This project uses existing, local resources and will be undertaken in a way that is consistent with the cultural understanding of the local community in Jumla and acceptable to local care-givers.

**Trial registration:**

Australia and New Zealand Clinical Trials Register, ACTRN12614000231640.

## Background

Chronic Suppurative Otitis Media (CSOM) is a common, preventable cause of deafness, chronic ill-health and, rarely, death in children in low resource countries. CSOM usually arises as a complication of untreated acute otitis media, which is almost universal in young children. Ear infections are so common, that they can seem normal and of low health priority [1, 2]. Acute ear infections are simple and inexpensive to treat, which can prevent CSOM, yet many children receive no assessment or intervention. Simple topical treatment with Ciprofloxacin ear drops has been found to be superior to both oral antibiotics and older combination drops [3–5]. Locally made Ciprofloxacin eardrops are widely and cheaply available in Jumla. CSOM is a disease of poverty and its social determinants. Low parental education level, low parental income, malnutrition, overcrowding, lack of clean water and sanitation are all associated with increased risk of CSOM [1, 6, 7]. The children most at risk of CSOM are also the ones with least access to health education and health care.

The World Health Organisation (WHO) has declared that a prevalence of CSOM greater than 4 % requires emergency measures [1]. At least 50 % of children with CSOM will have significant hearing loss, a global burden of 164 million people, 90 % of whom live in low resource countries, such as Nepal [1]. The most extensive recent prevalence survey in Nepal found that 7.6 % of children aged 5 to 13 years had CSOM [8]. Multiple smaller scale surveys have returned similar results [9–13].

Previous studies have established economic, socio-cultural and geographic barriers to care seeking for childhood illness in the developing world, including Nepal [1, 14–16]. Even in places where appropriate health services are available, they are not fully utilitised [17]. Community based interventions have been trialled to improve engagement with health services and decrease childhood morbidity and mortality [18–20]. The World Health Organisation has produced a primary ear care programme to educate and motivate the community about ear infections and the need to take action to prevent CSOM and hearing loss [21]. This programme is simple and can easily be adapted to cultural contexts and delivered in a socially acceptable setting. There have been few previous successful interventions aimed at prevention and early treatment of CSOM and no published data on the effectiveness of community education or primary ear care training for the community. Consequently, this trial tests the hypothesis that simple ear training can improve maternal practice and reduce the prevalence of the complications of acute ear infections.

## Methods/design

### Study aim

The overarching aim of our study is to improve the ear health of the children in Jumla, Nepal. In order to achieve our aim, our objectives include: improving the knowledge and practice of women regarding the ear health of their children, reducing the prevalence of CSOM and reducing the prevalence of other abnormalities of the tympanic membrane.

### Study design

Our study uses a cluster randomised trial design and is profoundly informed by our previous qualitative study (unpublished), consisting of in-depth interviews with women in Jumla, Nepal. Existing women’s self-help groups will be the unit of randomisation, or cluster. This is a suitable method for an intervention that takes place at the group level and is commonly used in community-based interventions [18, 19, 22–24]. Stratification will be done to avoid sampling bias, as power is better maintained than with matching. The 56 existing groups will be stratified into according to Village Development Committee and the remoteness of their location and distance to the road. Although all of these groups are in a remote location, distance to the road determines accessibility of health and other services. Following stratification, a random sample of 30 groups will be chosen for the study. Randomisation will be done using a computer generated random number sequence in Australia, by a member of the team (HW) not involved in data collection. The selection will then be communicated to the field team leader by internet or telephone. We will seek individual informed consent from each participant woman. After baseline data collection, groups will be randomly allocated to the intervention group and to the control group, stratified by geography. Randomisation will again be performed by a team member in Australia using a computer generated random number sequence and communicated to the field team leader by internet or telephone. The intervention will then be implemented over three consecutive regular monthly meetings of the self-help groups. International Nepal Fellowship is the only non-government organisation working directly with women in the two Village Development Committees, so it is unlikely that any co-interventions might contaminate the study. Women in Jumla are not generally mobile. A small number of women do migrate to India to work with their husbands and these women could be lost to follow-up but the numbers are likely to be very small. In the 2011 census, only 341 women in the entire district of Jumla were absent from their their homes [25]. Follow-up assessment at 12 months, repeating the women’s questionnaire and examination of the children’s ears will complete the study. Ethical approval has been granted by Human Research Ethics Committee, University of New South Wales (Ref# 13361) and Nepal Health Research Council (Ref # 1434).

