### Study setting

Our study is set in the isolated, mountain district of Jumla, Nepal. Nepal is a poor country with a Human Development Index 0.54, a rank of 145 out of 187 countries [26]. Jumla has an Human Development Index of 0.35, with a rank of 68 out of 75 districts in Nepal, making it one of the poorest and most disadvantaged districts in an already impoverished nation [27]. There has been little health research done in Jumla, although it was the first region to introduce community based management of childhood pneumonia [28–31]. Most of the population (88.7 %) live in small mountainside villages and eke a bare living from subsistence agriculture [32]. International Nepal Fellowship has agreed to host our research. They have been working in Jumla since 1978, initially offering outpatient and inpatient leprosy and tuberculosis care, later expanding their services to include a Community Development and Rehabilitation team. International Nepal Fellowship has a policy of social inclusion and poverty alleviation. They purposefully include women, low caste people and people living with disabilities in all of their programmes. International Nepal Fellowship has 56 women’s self-help groups, each comprising approximately 20 to 25 women, in two village development committee areas. The groups were formed following extensive community and local government consultation to find villages with the most poor and marginalised people. Consent and participation by villagers eventually led to the formation of the self-help groups. The groups have a distinct geographical catchment within the village and contain neighbours and extended family members. Each group has a monthly meeting facilitated by community workers. At the group meetings members discuss and participate in microfinance, income generation, health education and community mobilisation. Our research is set within these women’s self-help groups.

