### Sample size calculation

The sample size is calculated on the primary outcome. Using data extracted from questions in the previous qualitative study, sample size for an unclustered study with a 5 % two sided Type 1 error and 80 % power to detect a 25 % difference in mean questionnaire score, would be 114 women in each arm. Both Daly et al. in USA and Srikanth et al. in India found a very low level of knowledge about causes and risk factors for otitis media in mothers of young children [37, 40]. We anticipate a similarly low level in Jumla, and hypothesise that a 25 % increase would be modest and achievable. The cluster sizes are set at the size of the women’s groups which is around 20 women. To adjust for clustering, it is necessary either to establish an approximate intra-cluster correlation coefficient (ICC) or ρ, which measures the similarity of individual responses within clusters, in order to calculate the design effect (the number by which an individual trial must be multiplied to adjust for clustering) or to calculate the between cluster variability, k. These values vary and any estimate can only be approximate. Other studies on neonatal mortality in women’s groups in Nepal have found a very low ICC of 0.00644 [24]. Tielsch et al. [41] calculated a design effect of 1.23 with their study of supplements to prevent malnutrition in children. Mullany et al. [22] used a design effect of 2.0 for their study looking for a 25 % reduction in omphalitis in newborns in rural Nepal. Slightly further afield in Bangladesh, Aboud et al. [23] calculated an ICC of 0.03 for a responsive feeding and stimulation intervention to clusters of rural women and children. Pagel et al. [42] reviewed ICC for interventions around perinatal outcomes in low resource countries and found universally low ICC for maternal and neonatal mortality but higher ICC for other interventions such as skilled birth attendance. For example, in India and Bangladesh skilled birth attendance ranged from ICC 0.02-0.04. The Design Effect (DEff) is the number by which the sample size for an individual randomised controlled trial must be multiplied to give the equivalent power to a cluster randomised trial. The Design Effect also considers the number of individuals in each cluster *– m.* Using the equation DEff = 1 + (*m*-1) ρ, assuming ρ = 0.03, would give a DEff = 1.6, or 182 women per arm. Using the safe equation DEff = 1 + (m-1) ρ, assuming ρ = 0.05, would give a DEff = 1.95, or 223 women per arm. This would translate into 11 clusters per arm. To account for stratifying, we have added a conservative extra two clusters per arm, which would make 13 clusters per arm. To enable robust cluster analysis a minimum of 15 clusters is ideal. This will provide a generous total sample of approximately 600 women in 30 clusters, 15 in the intervention and 15 in the control arm.

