
### Statistical analysis

Analysis will be by intention-to-treat, all study participants will be included in the analysis, even if lost to follow-up. Analysis will be adjusted for clustering. Every effort will be made to have complete data but missing data will not be ignored in the analysis. Data will be checked and cleaned before being entered into Statistical Package for the Social Sciences. At baseline a comparison profile of both intervention and control groups will be provided. The primary and secondary outcomes - difference in mean questionnaire score and prevalence of CSOM - will be compared between the two groups. Data will be analysed at both individual and cluster level. Cluster level analysis is very robust and, with 15 clusters in each arm, individual level analysis, adjusted for clustering ought also to be very robust. For the primary outcome, a summary measure, the mean score of the questionnaire, will be calculated and then the intervention and control group compared for significance with a *t*-test at the cluster level. For individual level analysis, we plan to use mixed effects linear regression, which adjusts for the effect of clustering. The secondary outcome is a proportion, so we plan to analyse individual level data using logistic regression random effects model, using quadrature checks, which also adjusts for clustering. Since the age range is quite broad we will consider each standard age grouping in our analysis: under one year, under five years, and five years and over. We will also analyse duration of ear discharge as this is strongly correlated with prognosis. Covariates including socioeconomic status, education, caste, geography and number of household members will be considered.

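### Allocating 30 groups on geography alone leaves avoidable, mostly moderate, chance imbalance in baseline traits, although baseline data are collected before allocation

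*Protocol article*

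**What the plan says.** In the Protocol article, Study design first stratifies the pool of groups for sampling: "The 56 existing groups will be stratified into according to Village Development Committee and the remoteness of their location and distance to the road". Thirty groups are drawn. Then: "After baseline data collection, groups will be randomly allocated to the intervention group and to the control group, stratified by geography". The sequence is generated off site, by a team member in Australia. The Sample size calculation gives "15 in the intervention and 15 in the control arm".

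The section on the primary outcome measure places the questionnaire before allocation and names maternal education among its items. Caste is not in that list, which is given as examples. The section on the secondary outcome measure makes the children's ear examination part of baseline. A specialist reads the images later and has the last word on diagnosis.

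The Statistical analysis section compares mean scores with a cluster-level t-test, described without adjustment, and adds a mixed model for individual data. On covariates it says: "Covariates including socioeconomic status, education, caste, geography and number of household members will be considered". Baseline score and baseline CSOM are not in that list.

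**The concern.** Study setting describes groups with distinct catchments that "contain neighbours and extended family members". It is a fair inference, though not a statement in the protocol, that caste and schooling vary more between groups than within them. Their balance then depends mainly on how 30 units fall into two arms, not on about 600 women. Stratifying by place removes only the part of that variation that follows place.

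Most of the information needed for better balance is collected before allocation and then not used for it. Allocation cannot be redone. If the arms differ visibly at baseline, the planned t-test does not account for it, and choosing covariates after seeing the imbalance invites criticism. At stake are the precision of the comparison and how convincing its result will be.

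**Working it through.** **1. The protocol's own figures (Sample size calculation).** Inputs: "5 % two sided Type 1 error", 80% power, "difference in mean questionnaire score, would be 114 women in each arm", and a cluster size m set by "groups which is around 20 women".

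- Design effect = 1 + (m − 1) × ICC. With m = 20 and ICC 0.05: 1 + 19 × 0.05 = 1.95. Then 114 × 1.95 = 222.3, rounded up to 223 as stated.
- With ICC 0.03: 1 + 19 × 0.03 = 1.57, rounded in the protocol to 1.6. Then 114 × 1.6 = 182.4, stated as 182.
- No SD is given, so the planned effect is recovered by inversion: (1.960 + 0.842) × √(2/114) = 0.371 individual SD.

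**2. Chance imbalance in baseline score.** Variance of a group mean, in individual-SD units: ICC + (1 − ICC)/m = 0.05 + 0.95/20 = 0.0975. SD of the difference between arms: √(2 × 0.0975/15) = 0.114, which is 0.114/0.371 = 31% of the planned effect. Normal tails:

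- more than a quarter of the effect: 42% (ICC 0.03: 36%);
- more than half of the effect: 10% (ICC 0.03: 7%).

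These figures give no credit for geographic stratification. They would be lower if place explains part of the between-group variation.

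**3. Any group-level trait, in between-group SDs.** SD of the arm difference = √(2/15) = 0.365 if geography explains nothing. For one trait, the chance of a difference above 0.25, 0.5, 0.75 and 1 SD is 49%, 17%, 4% and 0.6%. For at least one of four independent traits, 1 − (1 − p)⁴ gives 93%, 53%, 15% and 2%.

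**4. Geographic stratification against constrained randomisation, by simulation.** Assumptions not in the protocol: four strata of 8, 8, 8 and 6 groups; geography explains 0, 25 or 50% of between-group variance; correlation between the four traits is 0 or 0.5. Each of 2,000 simulated trials had 1,000 stratified allocations. The constrained version draws one at random from the 100 best balanced. Ranges are over the six scenarios.

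| | Geography only | Constrained, best 10% |
|---|---|---|
| SD of arm difference | 0.26-0.37 | 0.10-0.15 |
| Given trait differs by >0.5 SD | 6-17% | about 0% |
| Any of four differs by >0.25 SD | 75-93% | 0.2-39% |
| Any of four differs by >0.5 SD | 17-53% | about 0% |

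The SD falls by more than half in every scenario; for example, 0.365 to 0.153 is a 58% reduction.

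**5. Baseline CSOM.** Prevalence 7.6% (Background: a national survey of ages 5 to 13). Assumed: 20-40 children per group and ICC 0.01-0.05. SE of the arm difference = √(2 × 0.076 × 0.924 × [1 + (m − 1) × ICC]/(15m)), where m is now children per group. At m = 40 and ICC 0.03 this is √(2 × 0.0702 × 2.17/600) = 2.25 percentage points. Over the whole range it is 1.8-3.0 points.

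**6. Power as planned.** At 15 groups of 20 per arm, ICC 0.05 and 28 degrees of freedom, the cluster-level t-test has 88% power for 0.371 SD.

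**The case against.** The strongest reply is that nothing is invalid. Under randomisation, chance imbalance neither biases the estimate nor raises the type I error. Between-group variation is already in the design effect, and power is 88%. Study design gives a reason for stratifying rather than matching. The mixed model allows covariates, and their final specification may properly sit in an analysis plan that is not shown. All of this stands. What it leaves untouched is the allocation method, which this document fixes and no analysis plan can change.

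Several stronger readings are tempting and should not be drawn.

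- **Large differences are likely.** Not shown: above 0.5 SD, the chance for any given trait is 6-17%. A caste example can look alarming. If 9 of 30 groups were mainly low caste (an assumption), unrestricted allocation gives a 6:3 or worse split 43% of the time. But the best possible split is 5:4, so 6:3 is one group away from it; 7:2 or worse has an 11% chance and 8:1 or worse 1.4%. The protocol's allocation is also not unrestricted.
- **The CSOM imbalance rivals the planned effect.** The 25% target belongs to the questionnaire score. No effect size is set for CSOM, so there is nothing to compare with.
- **Every balancing variable is ready before allocation.** The specialist's CSOM diagnosis is not stated to be complete by then, and caste is not named among the baseline questions, although its use as a covariate implies that it is collected.
- **The protocol calls caste, education and socioeconomic status prognostic.** It only lists them for consideration.

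It is also fair to say that adjusting for four group-level variables costs degrees of freedom: 28 − 4 = 24, before any terms for strata. The two-sided 5% critical value moves only from 2.05 to 2.06, so the cost is real but small.

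**Conclusion.** The point holds as a recommended improvement in precision and credibility, not as an error. Allocation is restricted on geography only, while more useful baseline information is collected first. Moderate imbalance on at least one of four relevant traits is likely. Serious imbalance on a particular one is uncommon, and a baseline-score gap above half the planned effect has about a 10% chance at ICC 0.05.

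A reader might infer that the trial's comparison is compromised. The documents do not support that: the randomised comparison stays unbiased and the t-test valid.

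The 0.371 SD effect follows from the stated 114 per arm. The simulation ranges rest on assumed strata, variance explained by geography and correlations. The CSOM figures rest on assumed numbers of children per group and ICC. How far a baseline-score gap carries through to follow-up depends on the correlation between the two surveys, which is not given.

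**What to change.** **If allocation has not yet taken place** (Trial status says only that data collection has begun), replace the allocation sentence in Study design with wording such as:

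*After baseline, the team member in Australia will generate many allocations of 15 and 15 groups within the geographic strata. The best-balanced 10% on group means of baseline questionnaire score and maternal education, share of low-caste women (if collected) and field-diagnosed CSOM prevalence will be retained, and one will be drawn at random. The retained set will be checked to confirm that no two groups are always, or never, placed in the same arm.*

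There is room for this restriction. With the assumed strata, the number of allocations is 70 × 70 × 70 × 20 = 6.86 million.

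**In either case**, state in Statistical analysis, before outcome data are seen, that:

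- baseline score enters the primary model, with the cluster-level comparison also adjusted for the group's mean baseline score;
- the group's baseline CSOM prevalence enters the CSOM model;
- any other variable used for balancing is included in both models.

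**Cost.** The programming is small and falls to the person who already runs the randomisation. The larger task is entering about 600 paper questionnaires and the children's examination sheets, and summarising them by group, before allocation. Balancing on CSOM uses a provisional field diagnosis, unless allocation waits for the image reading. A few cluster-level degrees of freedom are spent.
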